### Breaking the code

Code breaking will occur after completion of the trial unless it is necessary to break the code due to safety reasons. In the case of a serious adverse event or suspected unexpected serious adverse reaction, only the principal investigator (and the sponsor) has the right to unblind the given treatment to a patient in case of emergency. One set of emergency code envelopes will be kept by the sponsor at the coordinating centre (Karolinska University Hospital) in a locked facility. All recruited participants will be given contact details to the trial team including emergency contact 24 hours a day, 7 days per week. Emergency unblinding can occur at any time. Details of the unblinding will be documented.

### Outcomes

#### Mammographic breast density: primary outcome in part 1

Full-field digital mammography at baseline and after 12 months of treatment comprises mediolateral oblique and craniocaudal views of both breasts. Abnormalities will be evaluated on both views of each breast. In addition to visual judgement, a computer-based quantitative assessment will be performed. All mammograms will be pseudonymised so that the assessor will be unaware of the patient’s identity and type of treatment. The dense area on the right craniocaudal view image will be measured by using a commercial computer-assisted programme. A computer then records the number of pixels that fall within the defined areas according to the methodology described and used by us previously.^27^,^30^ Percentage change in mammographic density will be evaluated and compared between groups.

#### Breast cell proliferation: secondary outcome in part 1

Core needle breast biopsy from the upper lateral quadrant of the right breast will be taken after local anaesthesia at baseline and after 12 months of treatment. Ultrasound is used to identify areas with fibroglandular tissue. All women will be biopsied at the Mammography unit, Karolinska University Hospital. Tissue samples are paraffin-embedded and sectioned at 5 µm until analysis. Slides will be stained for the proliferation marker Ki-67 and other markers related to proliferation and apoptosis (caspase-3, p53 and bcl-2), and steroid hormone receptors. In addition to standard immunohistochemistry, a quantitative image analysis will be performed using a Leica microscope and Sony video camera connected to a computer with an image analysis system (Leica Imaging System, Cambridge, UK).^27 31^ Percentage change in breast cell proliferation will be evaluated and compared between the groups.

#### Endometrial assessment: secondary outcome in part 1 and primary outcome in part 2

The bleeding pattern will be registered by the patient throughout the study by a digital mobile application. Gynaecological examination including transvaginal ultrasound to determine endometrial thickness, as well as endometrial aspiration biopsy, will be collected at baseline and after 12 months of treatment. In part 1, endometrial histology and changes in proliferation markers, such as Ki-67, growth factors and markers related to apoptosis, will be compared between the randomised groups.^32^,^34^In part 2, the incidence of endometrial pathology (hyperplasia or cancer) will be examined in all participants allocated to 12 months of daily treatment with 100 mg mP in combination with 1 mg oestradiol. Endometrial histopathology will be evaluated according to a structured histological classification by two pathologists at the Department of Pathology, Karolinska University Hospital blinded to treatment and time of biopsy. In case of disagreement in interpretation, a third pathologist, also blinded, should be called on to make the final determination. The following histological classification will be used in both part 1 and part 2: no/insufficient tissue for evaluation, atrophic endometrium, inactive endometrium, proliferative endometrium, secretory endometrium, menstrual type, simple hyperplasia, complex hyperplasia, atypical hyperplasia and carcinoma.^32^

#### Vaginal and gut microbiome: secondary outcome

Vaginal and rectal microbiome will be characterised based on shotgun metagenomic sequencing and metabolomic profiling. DNA extraction will be performed with standardised and automated pipelines for vaginal^35^ and rectal samples.^36^ Taxonomical profiling will be based on metagenomic sequencing to identify important organisms on species/strain level as well as to characterise their functional information such as enzymes involved in metabolic pathways and antibiotic resistance. Untargeted metabolomic analysis of vaginal and rectal samples will be carried out using ultrahigh performance liquid chromatography-tandem mass spectroscopy.^37^ The absolute and relative abundance of different microbial species and diversity in the women before and after 12-month treatment will be evaluated and compared between groups.

#### Serum levels of hormones, growth and metabolic factors, lipid profile and coagulation factors

Venous blood samples in a fasting state will be drawn at baseline and after 12 months of treatment for determination of circulating hormones and growth factors (FSH, luteinising hormone, oestradiol, progesterone, testosterone, sex hormone-binding globulin and insulin-like growth factor I), the lipid profile (total cholesterol, high-density lipoprotein, low-density lipoprotein and triglycerides) and coagulation factors (antithrombin, factor V Leiden, factor II mutation, cardiolipin-ab, lupus anticoagulant, protein C activity, protein S free, activated partial thromboplastin time, fibrinogen, prothrombin complex and thrombocytes). Correlations between serum markers and primary outcome variables will be performed.

#### Depression, anxiety, quality of life and menopausal symptoms

Validated self-assessment questionnaires will be used for screening of mood disorders, quality of life and menopausal symptoms. The Patient Health Questionnaire (PHQ-9) is a tool for screening, diagnosing and measuring the severity of depression.^38^ The Hospital Anxiety and Depression Scale (HADS) is an instrument for detecting states of depression and anxiety in the setting of a hospital or medical outpatient clinic.^39^ Health-related quality of life is measured using the Psychological General Well-Being Index (PGWB).^40^ The Women’s Health Questionnaire (WHQ) measures menopausal symptoms.^41^ Changes in scores will be compared between the groups.

### Sample size calculation

#### Mammographic breast density: primary outcome in part 1

Based on data from the WHI study, it was shown that an increase in mammographic density by 1% during combined MHT corresponded to a 3% increase in risk of breast cancer.^42^ We estimated that a difference of at least 30% in treatment response between the groups would be clinically relevant. A power analysis based on our previous results,^27^,^30^ and assuming a 35% difference in treatment response, revealed that a patient material of 91 women/group would be sufficient to detect a significant difference in mammographic breast density between the groups at the 5% level (two sided) with 80% power. Considering the estimated rate of discontinuation and incomplete data (~30%), the target sample for this part of the study would be 260 patients.

#### Endometrial pathology: primary outcome in part 2

The reported 1-year background incidence rate for endometrial hyperplasia/cancer in postmenopausal women treated with authorised oestrogen/progestogen combinations is approximately 0%–1%.^18 19^ With a sample size of 300 women in the treatment arm mP+E, two or less women with serious adverse endometrial outcomes would result in an annual incidence of 0.67% or less with an upper bound of the one-sided 95% CI of 2.08% or less. Considering the estimated rate of discontinuation and incomplete data (~30%), the target sample for this part should be 390 patients, 130 women randomised to mP from part 1 and another 260 women from part 2.

The total number of patients in part 1 (n=260) and part 2 (n=260) will be 520.

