Endometrial hyperplasia is a strong risk factor for endometrial cancer.^45^ We will evaluate endometrial histology in both part 1 and part 2 of the trial, but the randomised part (n=260) is not powered for evaluation of endometrial hyperplasia and cancer, and therefore, this part will be comparing endometrial histology and proliferation between the two treatment groups as secondary objectives. The combination of 0.5 mg NETA/1 mg oestradiol (Activelle) is standard treatment with a well-known endometrial safety profile. In contrast, the combination of 100 mg mP/1 mg oestradiol has only been evaluated for endometrial safety in one previous study,^23^ and therefore, we found it important to study the incidence of endometrial hyperplasia and cancer of this treatment compared with the background incidence rate as a primary objective in part 2 of the trial.

A potential limitation of the study is the duration of treatment of 1 year. This could be regarded as short term, but previous studies have demonstrated that change in mammographic density by hormone treatment develops as soon as after a few weeks.^46^ Moreover, based on the estimated incidence rate of endometrial pathology (hyperplasia and cancer), 1 year should be sufficient for assessment of endometrial safety.^43^

The strengths of the study include the double-blind, multicentre, randomised design and the sufficient number of patients to assess the primary outcomes according to power calculations. Other strengths are blinded assessment of both mammographic density and endometrial pathology. Furthermore, secondary outcomes include a deeper investigation of the treatment effects on breast and endometrial tissue, as well as assessments of subjective symptoms and health-related quality of life by validated questionnaires. In addition, the treatment effect on the gut and vaginal microbiome will be studied. All data will be collected by a digital platform, which will facilitate the extraction and compilation of data.

The study is expected to provide increased knowledge about breast and endometrial safety with mP compared with progestin in continuous combination with oestrogen. The results can then be part of the basis for updated national and international guidelines for hormone treatment in menopause.

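### At the stated 30% loss, the part 2 target of 390 leaves 273 evaluable women, not the 300 on which the 2.08% upper bound rests

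*Protocol article*

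**What the plan says.** The part 2 paragraph of the Sample size calculation section (Protocol article) starts from 300 women: "With a sample size of 300 women in the treatment arm mP+E". For up to two events among them, it gives an incidence of at most 0.67%. The precision it claims for that scenario is an "upper bound of the one-sided 95% CI of 2.08% or less".

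It then allows for loss: "Considering the estimated rate of discontinuation and incomplete data (~30%), the target sample for this part should be 390 patients". The 390 are made up of "130 women randomised to mP from part 1 and another 260 women from part 2".

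The part 1 paragraph of the same section starts from 91 women per group and, with the same allowance of about 30% for discontinuation and incomplete data, concludes that "the target sample for this part of the study would be 260 patients".

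The Discussion lists among the strengths "the sufficient number of patients to assess the primary outcomes according to power calculations".

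**The concern.** The precision statement belongs to 300 women with a usable result. If about 30% are lost, the number enrolled has to be 300 divided by 0.70. The target of 390 is instead what results from adding 30% of 300 to 300. Taking 30% away from 390 does not return 300. Part 1 makes the allowance correctly, so two adjacent paragraphs treat one loss rate in two ways.

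Part 2 is a single-arm study with no hypothesis test described. Its primary outcome is reported as an incidence with a confidence interval, and the width of that interval is the only justification given for its size. If the loss occurs as assumed, a reader will expect a precision that the enrolled number does not provide, and the Discussion's claim of sufficiency rests on it.

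**Working it through.** **Inputs** (all from Sample size calculation, Protocol article)

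- Women on which the precision rests: 300
- Events in the planning scenario: up to 2
- Stated results: incidence 0.67%, one-sided 95% upper bound 2.08%
- Loss: about 30%, taken as 0.30
- Part 2 target: 390 = 130 (part 1) + 260 (part 2)
- Part 1: 91 per group, 182 in all, target 260

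**1. Reproduce the stated bound.** The exact (Clopper-Pearson) one-sided 95% upper limit for x events in n women is the 0.95 quantile of a Beta(x + 1, n − x) distribution. For x = 2 and n = 300 it is 2.084%, and 2/300 = 0.67%. Both match the plan, so the plan used this method with n = 300. Other methods for 2/300 do not match: one-sided Wilson 1.99%, one-sided Poisson 2.10%, two-sided exact 2.39%.

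**2. Reproduce the two targets.**

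| | n/(1 − 0.30) | n × 1.30 | Stated |
|---|---|---|---|
| Part 1, n = 182 | 260 | 237 | 260 |
| Part 2, n = 300 | 429 | 390 | 390 |

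Part 1 fits division and part 2 fits multiplication, both exactly. The plan does not write out either step, so the multiplication is inferred. The next step does not depend on it.

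**3. Apply the stated loss to the stated target.** 390 × 0.70 = 273, which is 27 short of 300. By source: 130 × 0.70 = 91 from part 1, the number part 1 itself plans for, and 260 × 0.70 = 182 from part 2.

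**4. Precision at each size** (exact one-sided 95% upper bounds)

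| Events | n = 300 | n = 273 |
|---|---|---|
| 0 | 0.99% | 1.09% |
| 1 | 1.57% | 1.73% |
| 2 | 2.08% | 2.29% |

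Two events in 273 women are an incidence of 0.73%.

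**5. Loss at which 390 would be enough.** 1 − 300/390 = 23.1%. If the part 1 arm ends with 91, as planned there, part 2 would have to supply 300 − 91 = 209 of its 260 women, a loss of 51/260 = 19.6%.

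**6. Sensitivity: 390 enrolled, two events** (evaluable number rounded down)

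| Loss | Evaluable | Upper bound |
|---|---|---|
| 20% | 312 | 2.00% |
| 25% | 292 | 2.14% |
| 28% | 280 | 2.23% |
| 30% | 273 | 2.29% |
| 35% | 253 | 2.47% |

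**7. Chance of a bound no higher than the stated 2.08%.** This allows at most two events with 300 women but at most one with 273. Binomial probabilities for true incidences within the plan's 0% to 1% background range:

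| True incidence | n = 300, at most 2 events | n = 273, at most 1 event |
|---|---|---|
| 0.5% | 81% | 60% |
| 0.67% | 67% | 45% |
| 1.0% | 42% | 24% |

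**The case against.** The best case for leaving the text alone has four parts.

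- **The sentence about 300 women is conditional and true.** With none or one event, 273 women still give a bound below 2.08%, so only the two-event edge fails. This stands as a limit on the claim. But the plan states its property for up to two events, and at 30% loss it does not hold there.
- **No decision rule is broken.** The article names no acceptance limit. The bound moves by 0.21 percentage points, and both values lie above the background range of 0% to 1%. This also stands: the shift changes no stated criterion. The figures remain the only justification for the size, and the plan's own loss assumption contradicts them.
- **The 273 may be pessimistic.** Under Discontinuing study treatment, women who stop early after at least one dose are due the end-of-study procedures, and Table 1 places an endometrial biopsy at that visit. Some of them would therefore contribute histology. That is fair, but the 30% explicitly covers incomplete data as well as discontinuation, and a biopsy taken early does not reflect 12 months of exposure. If the authors expect enough such biopsies to bring the loss down to 23%, the stated 30% is the wrong figure for this outcome.
- **All 390 could serve as the denominator,** as the Abstract's description of the safety population might suggest. Two events would then give a bound of about 1.6%. But this counts women without an end-of-treatment biopsy as free of disease and makes the loss allowance pointless.

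**Conclusion.** The concern holds. At the plan's own loss rate, 390 enrolled women give 273 evaluable. That is 27 fewer than the precision statement needs, or 39 fewer enrolled (429 − 390). In the two-event scenario the incidence is 0.73% instead of 0.67%, and the one-sided exact 95% upper bound is 2.29% instead of 2.08%. A bound within 2.08% then allows one event, not two.

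This rests on reading the 30% as the share of enrolled women without a usable endometrial result, which is how part 1 uses it, and on the exact method that reproduces the plan's own 2.08%. Rounding in the phrase about 30% does not rescue the target, because loss would have to be 23.1% or less. The effect on precision is modest, but it concerns the sample size of a primary outcome and should be corrected.

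**What to change.** In the part 2 paragraph of Sample size calculation, make one of these changes:

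- **Keep 390 and restate the precision,** for example: *Allowing for 30% loss, 390 women give about 273 evaluable. Two or fewer events then correspond to an incidence of 0.73% or less, with a one-sided exact 95% upper bound of 2.29% or less.*
- **Keep 300 and state the condition:** 390 enrolled women provide 300 evaluable only if loss does not exceed about 23%, with the reason for expecting a lower loss than in part 1.

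In the Discussion, tie the statement about sufficient numbers for part 2 to the corrected figures.

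The cost is wording and a slightly less favourable published figure, with no extra patients. Keeping both 300 evaluable and 30% loss would instead require 429 women: 299 in part 2 beside the 130 from part 1, or 260 + 299 = 559 in all instead of 520. The correction does not require that.

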### Data statement section

A digital platform is used for data entry by the patients (questionnaires and eventual bleeding) and the study personnel. All patient data are encoded according to a code list, which is only available to the researchers in the project. The results are processed after the deidentification.

#### Statistical analysis

Analyses of primary and secondary outcomes will be based on an intention-to-treat (ITT) population (all subjects who have received at least one dose of study drug with a baseline evaluation meeting the entry criteria), as well as per-protocol population (subjects who have completed the study without major protocol deviations). The safety analysis population will comprise all patients who received at least one dose of the study drug.

The primary outcome variable mammographic breast density (part 1), expressed as percentage, will be compared between and within groups using the mixed model procedure with subjects as a random factor, and treatment (mP+E and NETA+E), time (baseline and exit) and treatment×time as fixed factors. Differences between groups will be evaluated by the interaction treatment×time, and differences within groups by the factor time, by holding the other factor (treatment) fixed.

Incidence of endometrial pathology (hyperplasia or cancer) in the mP+E group as endometrial safety (part 2) and based on histopathology will be expressed as incidence rate and 95% CI, in line with the European Medicines Agency guidelines.^43^

The secondary outcome variables (breast cell proliferation, endometrial cell proliferation, endometrial thickness using ultrasound, gene and protein expression of growth factors and apoptosis markers in breast and endometrial tissue, vaginal and gut microbiome, blood levels of serum hormones, growth and metabolic factors, lipid profile, and coagulations factors) will be analysed using the mixed model procedure with the same factors as above. In case of positively skewed distributions of these variables, log transformation will be performed prior to the analysis.

The Mann-Whitney U test will be used to compare the groups with respect to the changes in the PHQ-9, HADS, PGWB and WHQ and the Wilcoxon matched pairs test for changes in these variables within the groups.

If missing data occur in the ITT analysis, the method last observation carried forward (LOCF) will be used. Assuming missing data occur at random, patients with missing data can be included in the mixed model analysis, otherwise, we use the LOCF procedure. Correlations will be assessed by Spearman’s rank correlation test. A p<0.05 will be considered significant.

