### Exclusion criteria

A history or risk factors for breast cancer, breast cancer in situ or abnormal mammogram at baseline as assessed clinically by a radiology expert.A history or risk factors for endometrial cancer or hyperplasia or abnormal/proliferative endometrial biopsy at baseline.Vaginal bleeding.Any concomitant medical treatment except for well-controlled hypertension, non-insulin-treated type 2 diabetes, asthma and hypothyroidism.History or the presence of or risk factor for cardiovascular disease including thromboembolic disorder or cerebrovascular disease.History or the presence of liver and gallbladder disease, familial hyperlipidaemia, epilepsy or classical migraine with aura.A history or the presence of clinically significant depression or other psychiatric disorder that might in any way compromise the performance of the trial or undermine its scientific validity.Porphyria, systemic lupus erythematosus and otosclerosis.Current use of MHT or local oestrogen treatment.Alcohol and/or drug abuse.Clinically significant findings on physical and/or gynaecological examination at baseline.Hypersensitivity to any of the study treatments.

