### Discontinuing study treatment

Subjects may be discontinued from study for any of the following reasons:

Development of exclusion criteria during the course of the study.Serious adverse event.Significant protocol violation.Unacceptable toxicity.Failure to comply with study evaluations/visits which would prevent evaluation of drug compliance and supply.Other conditions for which, in the investigator’s opinion, it is in the subject’s best interest to be withdrawn from the study.

When a subject withdraws from the study, the reason for the withdrawal shall be recorded. Any subject who prematurely terminates participation and has received at least one dose of study drug will undergo end-of-study procedures. If study participation is terminated due to an adverse event possibly related to the study drug or study examinations, the subject must be followed up according to the medical judgement of the investigator.

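### The completers-only per-protocol set can drop a woman from the Part 2 endometrial incidence because she had the outcome

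*Protocol article*

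**What the plan says.** Protocol article, Statistical analysis: "Analyses of primary and secondary outcomes will be based on an intention-to-treat (ITT) population", defined by at least one dose and an eligible baseline evaluation. The same sentence adds a "per-protocol population (subjects who have completed the study without major protocol deviations". The Part 2 primary outcome is the "Incidence of endometrial pathology (hyperplasia or cancer) in the mP+E group as endometrial safety (part 2) and based on histopathology", reported with a 95% confidence interval. No separate analysis set is given for it.

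Discontinuing study treatment: "Subjects may be discontinued from study for any of the following reasons", and the list begins "Development of exclusion criteria during the course of the study.Serious adverse event". Women who stop early after at least one dose are to have the end-of-study procedures, and Table 1 includes an endometrial biopsy among these.

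Exclusion criteria: "A history or risk factors for endometrial cancer or hyperplasia or abnormal/proliferative endometrial biopsy at baseline".

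Outcomes, endometrial assessment: "endometrial aspiration biopsy, will be collected at baseline and after 12 months of treatment". The Part 2 incidence is to be examined in all women allocated to the mP combination.

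**The concern.** Taken together, these sections make the Part 2 event a reason for possible discontinuation, and discontinuation a reason for leaving the per-protocol set. Membership of that set then depends on the safety outcome being measured. Each woman lost in this way is a case. She takes one event out of the numerator and only one woman out of the denominator, so the estimate falls.

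An early diagnosis is plausible. Bleeding is recorded throughout by a mobile application, and there are visits at 3, 6 and 9 months, so bleeding could lead to a work-up before month 12.

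What is at stake is an accompanying estimate for a rare outcome. The sample size section reasons in terms of two or fewer events, so one missing case changes the figure visibly. The Introduction says that observational data point to a higher endometrial cancer risk with mP than with progestins, so a downward bias runs in the reassuring direction.

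**Working it through.** **Step 1. Follow one woman through the rules.**

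| Stage | Section | Consequence |
|---|---|---|
| Hyperplasia or cancer diagnosed before month 12 | Exclusion criteria | She now meets an exclusion criterion |
| "Development of exclusion criteria during the course of the study" | Discontinuing study treatment | She may be discontinued |
| Discontinued, so not a completer | Statistical analysis | Outside the per-protocol set |
| At least one dose, eligible baseline | Statistical analysis | Still in the intention-to-treat and safety sets |

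A woman whose lesion is found at the month-12 biopsy after full treatment is a completer and stays in the per-protocol set. Only earlier diagnoses followed by discontinuation are lost.

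**Step 2. Reproduce the plan's own figure.** Sample size calculation, endometrial pathology: n = 300, x = 2, incidence 0.67%, one-sided 95% upper bound 2.08%. The exact (Clopper-Pearson) one-sided upper limit is the 0.95 quantile of a Beta(x + 1, n − x) distribution. For x = 2 and n = 300 this is Beta(3, 298), which gives 2.084%. The plan's figure is reproduced.

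**Step 3. Remove k early cases.** Let x be all cases among 300 women who would otherwise qualify. The per-protocol set then shows (x − k)/(300 − k). The documents give no value for k, so it is an assumption and a range is shown. Upper limits use the Step 2 formula.

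| All cases x | Cases counted whenever diagnosed | k = 1 lost | k = 2 lost |
|---|---|---|---|
| 2 | 2/300 = 0.67% (2.08%) | 1/299 = 0.33% (1.58%) | 0/298 = 0% (1.00%) |
| 3 | 3/300 = 1.00% (2.56%) | 2/299 = 0.67% (2.09%) | 1/298 = 0.34% (1.58%) |
| 4 | 4/300 = 1.33% (3.03%) | 3/299 = 1.00% (2.57%) | 2/298 = 0.67% (2.10%) |

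With k = 0 the estimates are unchanged.

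**Step 4. Direction.** For 1 ≤ k ≤ x and x < n, (x − k)/(n − k) is smaller than x/n, because x(n − k) − n(x − k) = k(n − x) > 0. Losing cases in this way cannot raise the per-protocol incidence.

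**The case against.** Several objections limit the point.

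- **Discontinuation is permissive.** The plan says women may be discontinued, and it does not define study completion further. A diagnosed woman is a candidate for exclusion from the per-protocol set and is not certain to be excluded. This stands.
- **Most events should be found at exit.** Biopsies are scheduled only at baseline and month 12. A reader might infer that the per-protocol analysis omits all the events that Part 2 is meant to count. The documents do not support that, since month-12 cases in completers are kept.
- **Intention to treat.** A reader might infer that an early diagnosis also has no route into the intention-to-treat numerator. That is not supported either. Incidence is to be examined in all allocated women, those who stop early have the end-of-study biopsy, and the outcome rests on histopathology without restriction to the month-12 sample. What remains is a lesion treated before the exit biopsy, which is detail commonly left to the full protocol or analysis plan.
- **No pass/fail rule.** The sample size section describes precision. It is tempting to call three events a failed benchmark that a lost case turns into a success, but the plan states no such criterion.
- **Per-protocol need not look better than intention to treat.** The per-protocol set also sheds women without an event. Suppose 30% of 390 are lost, leaving 273, and one of three cases is dropped. Per-protocol then gives 2/272 = 0.74% (upper limit 2.30%), against 3/390 = 0.77% (1.98%) by intention to treat. The per-protocol upper limit is the less reassuring one. This is a fair limit on any claim of false reassurance relative to intention to treat. It does not remove the bias within the per-protocol analysis, because keeping the case would have given 3/273 = 1.10% (2.82%).

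It could also be said that set definitions belong in the analysis plan. Here the article states the definition and applies it to the primary outcomes, so the objection is to a rule that is fixed and not to one that is absent.

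**Conclusion.** The point holds for the per-protocol analysis of the Part 2 endometrial outcome. As written, the rules allow a woman to leave that analysis because she had the event, and for such cases the per-protocol incidence is biased downward.

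The size depends on an assumed number of diagnoses before month 12 that are followed by discontinuation. In the three-case illustration, one lost case lowers the estimate by a third, from 1.00% to 0.67%, and the upper limit by about half a percentage point. The calculation takes the plan's 300 women as the per-protocol set before cases are lost.

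The intention-to-treat and safety sets do not require completion and keep these women, so the Part 2 primary result is not invalidated. This is a should-fix, not a must-fix.

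**What to change.** Add an exception for the endometrial outcome to the per-protocol definition under Statistical analysis. Keep in its numerator and denominator every woman with histologically confirmed hyperplasia or carcinoma at any time after the first dose, whether from a scheduled, early-termination or clinically indicated biopsy, provided she had no major protocol deviation unrelated to the event. Require completion only of women without an event.

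This takes one or two sentences and changes no treatment, visit or scheduled procedure. Reports of clinically indicated biopsies would have to be collected where they exist. The downside is that the per-protocol incidence may be slightly less favourable.
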